**E. PROTECTION OF HUMAN SUBJECTS**

1.  TARGET POPULATION:

Individuals ≥12 months post treatment for colorectal cancer (n=40), who are over the age of 18 and meet the criteria for sarcopenia will be eligible to participate. About 90% of those who get colorectal cancer are older than 40, and in the rare instances of a colorectal cancer diagnosis under the age of 18, cancer risk and survival is not as strongly linked to lifestyle factors such as physical activity. In addition, treatment strategies and subsequent side effects also differ between child and adult survivors of cancer. Furthermore, the proposed resistance exercise protocols are designed for adults, and may not be appropriate for children. There will be no upper limit placed on age. About a third of the individuals who are diagnosed with colorectal cancer are 65 years or older. Therefore, we anticipate the majority of our subject population will be mid-life and older adults. The investigative team has expertise working with adults and older adults. Dr’s [name] and [name] have experience conducting interventions with older adults living with and without cancer, ranging from 18-85. In addition, as medical oncologist Dr.’s [name] treats patients ranging from 18 years old to end of life. Depending on the age distribution of participants who enroll, age may be considered as a covariate in analyses as needed.

Twelve months post treatment or greater was chosen to allow full recovery from the acute side effects of treatment that might influence exercise tolerance. Specifically, the SARC-F questionnaire will be used to screen individuals. The SARC-F is a self-administered questionnaire used to determine the level of difficulty experienced in 5 components comprising the strength, assistance in walking, rising from a chair, climbing stairs, and history of falls; a score of 0–2 points is assigned for each item. The total score ranges from 0 to 10, with scores of ≥4 points indicating the risk of sarcopenia. Participants will be excluded if they 1) are receiving active treatment for their cancer; 2) have a any contraindication to exercise participation; 3) have been participating in structured resistance exercise 2 or more times per week for the past 6 months; 4) are currently taking supplements containing creatine for 4 weeks prior to the start of the RCT, or 5) are receiving medications that might alter body composition (metformin, corticosteroids etc.).

A convenience sample (n=40) will be recruited to determine the feasibility of the intervention. The rationale for this is in line with recommendations from Julious et al (2005) that justify an n=12 as a minimum based on feasibility, gains in precision surrounding the mean and variance, and ability to estimate parameters for future studies.^103^ Consequently, given that our study has two arms, and in line with other exercise oncology trials in anticipation of an ~75% retention rate, we aim to recruit 20 individuals per arm to participate in full study activities.

2. RECRUITMENT PLANS:

Recruitment will occur in collaboration with two healthcare partners (PRISMA Health and South Carolina Oncology Associates, [SCOA]). SCOA is a medical and radiation oncology practice affiliated with an ACOS-approved Integrated Network Cancer Program in central South Carolina. PRISMA Health-Midlands provides multidisciplinary cancer care in Columbia that is a part of the larger PRISMA Health system. Participants will be recruited by 1) use of cancer registry data bases at local health care system’s cancer programs to prepare personalized invitations, and 2) outreach with various cancer support groups and organizations. We will also request a partial HIPAA waiver from the cancer clinics to recruit from patient lists of contact information. Specifically, the covered entity (Prisma), will provide us with a secure list of individuals previously treated for colorectal cancer, and their PHI. This is one of our strongest methods of recruitment and are currently using it in several ongoing studies. From these lists, we will send an initial introductory letter to eligible patients from their oncology provider with information about the study. There will be a number to call if they do not wish to be contacted by study personnel. After a wait time ~ 2 weeks, study staff will begin contacting the list of potential participants. At initial contact, study recruiters will provide a detailed account of the study and its procedures, answer any questions, ascertain interest, and, if interested, schedule the baseline visit.

Based on our recruitment goals and the proportion of individuals we anticipate being interested (~50%) and eligible (~50% of interested individuals), we will mail flyers and invitations in batches of 200. We will schedule mailings to occur approximately every 4-6 weeks until recruitment goals are met. If recruitment numbers are insufficient, we will increase both the size and frequency of mailings. In the event that recruitment numbers are insufficient, we will work more closely with oncologic and medical providers to promote participation in the study. Moreover, we will closely monitor the response to mailings and adjust our efforts accordingly. Specifically, mail flyers and invitations will be mailed in batches of 200. We will schedule mailings to occur approximately every 4-6 weeks until recruitment goals are met. If recruitment numbers are insufficient, we will increase both the size and frequency of mailings. Further, we will pursue more direct approaches of visiting colorectal clinics, cancer support groups, churches etc. Based on the prior work of our team in the area of cancer survivorship, we are confident these strategies will result in the recruitment of our desired number.

Individuals will be contacted by study staff and will be provided detailed information on the study purpose/aims, protocol, potential benefits and risks and answer further eligibility questions. If a participant meets initial eligibility criteria, they will be directed to an online Physical Activity Readiness Questionnaire (PARQ+; www.eparmedx.com) to ensure safety for exercise and determine whether physician clearance is required. Individuals who are eligible and remain interested will be asked to provide informed consent to participate prior to any study activities. This method of recruitment has proved successful in our prior exercise oncology trials.

3. EXISTING DATA/SAMPLES:

*N/A*

4. CONSENT/ASSENT

The following processes for consent will be conducted as follows:

- Mailings will be sent to potential participants that include a description of the study, it’s purpose, anticipated benefits and risks. The mailing will include a link to provide information for study staff to contact them.
- Once connected, a member of the study team will undergo an initial phone screening with individuals to provide a brief overview of the study, reinforce the anticipated risks and benefits, and that participation is completely voluntary. The phone screening will also include questions regarding the eligibility criteria to determine if the participant is suitable and eligible for the trial.
- Individuals who are interested and eligible will then be provided with further details regarding study participation and scheduled for a baseline assessment. Individuals will be emailed a copy of the informed consent form to review prior to arrival at the lab for baseline testing.
- Once participants arrive for baseline testing, a member of the study team will review the consent form in detail and answer any further questions participants might have. Every effort will be made by study staff to ensure the informed consent is understood in its entirety prior to signing. At this point, individuals will also be reminded that participation is completely voluntary, and that withdrawal is allowed at any point in the study without penalty.
- Individuals will be provided asked to provide “yes” or “no” options to consent to participate in the study.
- The signed document will be collected and catalogued by trained research staff.

5. POTENTIAL RISKS

**Potential Risks.** There are no foreseeable major risks or side-effects associated with participation. However, as is the case with anyone who exercises, participation in the exercise intervention may result in mild discomfort and muscle soreness. There is also the possibility of muscle pulls or strains associated the exercise program, common to any type of physical activity. In order to minimize these risks participants will perform an adequate warm-up and cool-down before and after any exercise bout, be comprehensively instructed on the correct lifting technique, thoroughly familiarized with the movements involved in this investigation and supervised at all times by qualified professionals. If participants experience discomfort, soreness, or any issues with their prescribed exercise, the exercise prescription will be modified accordingly. Risk of falling may exist in the performance of some tasks, however, participants will be closely supervised to minimize the risk of a fall occurring. Furthermore, during exercise it is possible to experience symptoms such as shortness of breath, abnormal blood pressure, fainting, light-headedness, muscle cramps or strain, nausea, and in very rare cases heart rhythm disturbances or heart attack. These potential risks are common to any form of physical activity. During exercise training in other clinical populations, such as cardiac rehabilitation, rates of serious adverse events are very low at 1 in 49,565 patient training hours. Participants may also experience some anxiety in answering the items in the questionnaires.

Creatine is one of the most widely researched supplements, with over 1,000 studies confirming its safety in a variety of populations. As such, the risks of any possible side effects are minimal. However, participants receiving creatine might experience some mild gastrointestinal disturbance. The most commonly reported gastrointestinal disturbance is a mild stomach ache, or excess gas/bloating/loose stool. These side effects have been previously reported but occur in less than 5% of individuals supplementing with creatine. If individuals experience gastrointestinal distress, we will monitor the situation and they will be advised to stop supplementation if necessary. Due to the rarity and mild nature of symptoms, we don’t anticipate any lasting adverse reactions.


**Protection Against Risk.** The risk of adverse events with exercise will be minimized by the supervision of exercise sessions by trained exercise physiologists on the study team. Further, the exercise sites have detailed emergency action procedures in place in the unlikely event that medical assistance is needed. These procedures include: 1) contacting emergency services (i.e., calling 911), 2) administering first aid, cardio-pulmonary resuscitation (CPR), and automated external defibrillation (AED) as appropriate, and 3) managing the situation until emergency services arrive. All staff are required to have current CPR and AED certification. Emergency action procedures are reviewed and practiced on a quarterly basis.

All survey/questionnaire responses will be kept strictly confidential. Participants will be informed that if they do experience discomfort or anxiety in filling out the questionnaire, they can choose to stop the assessment. If our study identifies that a participant is experiencing significant distress, he/she will be contacted, and their permission will be sought to inform their GP or cancer specialist so that referral to appropriate services can be made. Participants are asked to notify study staff immediately if they experience discomfort in answering the questionnaire questions. Study materials and data will be coded with numeric identifiers and will be accessed only by the PI. Staff will be trained in human subjects and confidentiality issues and procedures. Study materials and data will be kept in secure computer files and file cabinets at the Arnold School of Public Health, University of South Carolina.

**Adverse Event** The PI ([name]) will be responsible for monitoring and reporting all adverse events and unanticipated problems. Trained exercise professionals supervising each session minimizes the risk of exercise-related adverse events. Specifically, participants will be monitored for any adverse effects, and other disease-related or exercise-related adverse events using adverse event logs across each patient’s on-trial period, throughout the testing and training sessions. However, we will record and report adverse events in accordance with the CONSORT guidelines. Further, adverse events and unanticipated problems will be documented in accordance with the University of South Carolina’s standards and reported to the Institutional Review Board. Specifically, if an unexpected death occurs, a report will be sent to the Office of Research Compliance immediately. Serious, unexpected events will be reported within 48 hours, and all others within 10 working days. Adverse events will be recorded, including a description of the event, its relation to the intervention (not related, unlikely, possibly, probably, definite), its level of seriousness (i.e. non-serious, required hospitalization, resulted in persistent disability, life-threatening, or resulted in death) and its intensity (mild, moderate, severe, life-threatening). Additionally, the participant will be referred to their general practitioner or specialist, as appropriate for a medical assessment of any adverse event.

6. POTENTIAL BENEFITS:

**Potential Benefits of the Proposed Research to the Subjects and Others.** We believe the potential benefits of participating in this research are quite large. Specifically, individuals will receive 3 months of supervised, individualized exercise training that is specifically designed to improve strength, physical function and health-related quality of life. Moreover, participants will gain a better understanding of how to participate in and progress their exercise safely and effectively. Participants randomized into the supplement group may experience additional benefits in strength, physical function and body composition.

**Importance of the Knowledge to be Gained.** The potential knowledge gained from the proposed project is significant. Specifically, we will be one of the first to specifically implement an intervention targeting sarcopenia in individuals treated for colon cancer. We anticipate that the exercise and nutritional supplementation intervention will yield meaningful improvements in muscular strength, physical function, and body composition. If successful, our findings can offer information on a potentially low-cost therapeutic strategy that can offset the burden of cancer. Further, give the high prevalence of sarcopenia in individuals with cancer, our findings have the potential to support research in other patient populations. The information gained from the exploratory analysis of muscle signaling and mitochondrial health is potentially extremely important. This will be one of the first studies in humans to investigate the long-term effects of cancer treatments on the molecular regulation of muscle mass and how this may impact the response to treatment.

7. CONFIDENTIALITY

Data collected will be de-identified and coded. Each study participant will have a unique study identification code created following informed consent which will comprise two random letters and a consecutive number generated after consent. Data will be and kept electronically, in a password locked folder, on a password locked computer, accessible only by the investigators and designated research staff and will be held in the department of Exercise Science. At the completion of every data collection session, any physical documentation will be stored in a secure filing cabinet with restricted access in a private office in the Department of Exercise Science. All of this information will be held in these secure locations on campus (with password-protection or key-lock access); and will not be stored outside the University. All paper-based records will be stored in a locked filing cabinet with restricted access in a private office for a minimum of 3 years.

Participants will be provided with an explicit description of plans to share any data they contribute, and how their privacy and confidentiality will be protected. All de-identified data and code for analyses will be made available as soon as possible with publication of the primary outcome paper. The dataset will include demographic information, and physiological and psychosocial measures outlined in the proposal. We will make the de-identified data and associated documentation available to users only under a data-sharing agreement that provides for: (1) a commitment to using the data only for research purposes; (2) a commitment to securing the data using appropriate computer technology; and (3) a commitment to destroying the data after analyses are completed. Only researchers from universities, colleges, and research organizations, as determined by the Sponsored Awards Management office at the University of South Carolina, through a formal review process, will be provided these data.

8. COMPENSATION:

A $25 gift card will be given to participants for completing the baseline assessment. A $75 gift card will be given to participants for completing the follow-up assessment. Therefore, total rumination for participants who complete baseline and follow-up assessments will be $100.

Participants will also be offered a $50 incentive to receive an optional muscle biopsy at each assessment timepoint. Therefore, the total rumination for participants who complete both timepoints and receive a muscle biopsy at each timepoint is $200.

9. WITHDRAWAL:

Participants will be informed that their participation in this research is completely voluntary and made to understand that they are allowed to withdraw from the study from any time, without justification. All participants will be asked to inform a member of the study team of their decision and reason to withdrawal but will be informed that their withdrawal will not affect their relationship or any future opportunities to participate in research with the university. No additional information will be collected after an individual withdraws, through data collected up until the point of withdrawal will be used in analyses and interpretation of results.

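### Data collection stops at withdrawal with no safety exception, so an adverse event still open at that point cannot be followed to its outcome or final seriousness

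*Protocol*

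**What the plan says.** Section E.9 (Withdrawal) lets participants leave at any time without giving a reason, and then states the rule: "No additional information will be collected after an individual withdraws". The same sentence keeps what came before: "data collected up until the point of withdrawal will be used in analyses and interpretation of results". The section also provides that "All participants will be asked to inform a member of the study team of their decision and reason to withdrawal". It contains no clause on safety.

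Section E.5 (Potential Risks, paragraph on adverse events) sets out the safety record. Events are captured "using adverse event logs across each patient’s on-trial period, throughout the testing and training sessions". Each event is described and graded for relation to the intervention, for intensity and for "its level of seriousness (i.e. non-serious, required hospitalization, resulted in persistent disability, life-threatening, or resulted in death". On reporting: "Serious, unexpected events will be reported within 48 hours, and all others within 10 working days"; an unexpected death is reported at once. Finally, "the participant will be referred to their general practitioner or specialist, as appropriate for a medical assessment of any adverse event". Nothing says that the result of this assessment returns to the trial, or that an open event is followed until it ends.

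In section A, adverse events are one of the four components of primary aim 1(a). The hypothesis there is that none will occur, and trial success depends on the feasibility outcomes being achieved.

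**The concern.** Some seriousness levels in E.5 cannot be assigned when an event starts. Persistent disability needs time to establish, and hospitalization or death may come days or weeks after onset. The medical referral also yields its information later. If the person withdraws in between, E.9 bars the team from asking, and E.5 offers no second route because its logs end with the on-trial period.

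The gap is selective. It falls on people who leave with an event unresolved, and for them the grade on file is the one known at departure. A worsening after that day is not recorded, so any resulting error in seriousness is towards too mild a grade. This pilot is meant to inform a larger trial, and its safety record is part of what is carried forward. A later SAP cannot repair the gap, because it cannot analyse data that the protocol forbids collecting.

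**Working it through.** The protocol gives no figure for adverse events at withdrawal, so there is nothing to reproduce. The check is a reading of E.5 against E.9, followed by an illustration of scale.

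**Step 1. What is and is not recorded, by the state of the event at withdrawal**

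| State of the event | Recorded under E.5 and E.9? |
|---|---|
| Began and resolved before withdrawal | Yes, in full if logged |
| Began before withdrawal, still open | Onset, relation, intensity and seriousness as known at departure: yes, if logged. Later course, referral result, later rise in seriousness: no |
| Began before withdrawal, not yet reported to staff | Only if the person gives it as the reason for leaving; the reason is requested but need not be given |
| Began after withdrawal | No |

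Only the first row is safe in all respects. No other section of the protocol makes an exception for the remaining rows.

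**Step 2. How many participants could be affected**

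Inputs from the protocol: 40 participants, 20 per arm (section E.1); retention of at least 75% (section A); retention defined as returning for follow-up testing (section D, Primary Outcome).

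- Losses tolerated by the target: 40 × (1 − 0.75) = 10.
- These 10 are people who do not return for testing. They include people who lose contact or miss the visit, and E.9 does not apply to those people. The number of formal withdrawals is therefore at most 10 at this retention and may be lower.

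Let *m* be the number of formal withdrawals and *s* the share of them with an open event. The expected number of cut-off events is *m* × *s*, and the chance of at least one is 1 − (1 − *s*)^*m*, treating participants as independent. Neither *m* nor *s* is in the protocol. Both are assumed here: *m* = 10 if every loss is a withdrawal, *m* = 5 if half are.

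| *s* (assumed) | *m* = 10: expected | *m* = 10: at least one | *m* = 5: expected | *m* = 5: at least one |
|---|---|---|---|---|
| 5% | 0.5 | 1 − 0.95^10 = 40% | 0.25 | 1 − 0.95^5 = 23% |
| 10% | 1 | 1 − 0.90^10 = 65% | 0.5 | 1 − 0.90^5 = 41% |
| 20% | 2 | 1 − 0.80^10 = 89% | 1 | 1 − 0.80^5 = 67% |
| 30% | 3 | 1 − 0.70^10 = 97% | 1.5 | 1 − 0.70^5 = 83% |

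The table restates its assumptions. It shows that one or more cut-off events is possible in a trial of this size, and it does not estimate how much is under-recorded. A cut-off event is also not necessarily one whose grade would have risen.

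**The case against.** The case for leaving the text alone has real force.

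- **The record is not empty.** A reader might infer that a person who leaves because of an injury has no recorded course or seriousness. The protocol does not support that: everything logged up to departure is kept and used, and the reason for leaving is requested. This objection stands, and the loss is confined to what happens afterwards.
- **Trial success is not altered for logged events.** A reader might infer that the rule lets the trial pass its safety criterion when it should fail. The hypothesis is a count of zero, so an event that prompts withdrawal and is logged already breaks it, and its later course cannot change that. This also stands.
- **The reporting deadlines can be met.** E.5 asks for reports within fixed times, and these can be filed on what is known. It sets no duty to follow events to resolution. Its on-trial window is consistent with E.9, so the two sections do not flatly contradict each other. This stands too. The difficulty is that E.5 asks for grades and triggers a referral whose results E.9 then puts out of reach.
- **A side effect is not a withdrawal.** For gastrointestinal distress, E.5 says "we will monitor the situation and they will be advised to stop supplementation if necessary", and discomfort with exercise leads to a modified prescription. Neither is described as leaving the study, so the affected group is smaller than all who have an event.
- **Serious events are expected to be rare.** E.5 cites 1 serious event in 49,565 patient training hours in other clinical populations. With 40 × 30 = 1,200 sessions, assumed to last one hour each, that gives 1,200 / 49,565 = 0.02 events. The rate comes from a different population and covers exercise training only, so it lowers the expectation without settling it.
- **Stopping collection protects the participant.** That is right for anyone who refuses contact. It is no reason to bar contact with those who would agree to it.

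None of these points supplies a route for the later course of an open event. The consent form is not available here, so it is unknown whether it already permits safety contact. E.9 as written would bar such contact in any case.

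**Conclusion.** The point holds in a limited form. Following E.9 as written, the later course, the referral result and any later rise in seriousness of an event open at withdrawal cannot be collected, and events starting after withdrawal are missed. Seriousness may be understated as a result. It is not shown that harm is in fact under-recorded: that depends on how many people formally withdraw, how many have an open event, and how many of those events worsen, and the protocol gives none of the three. The only bound it offers is that up to 10 of 40 may be lost at 75% retention. For orientation, one event regraded in an arm of 20 moves that arm's proportion by 1/20, or 5 percentage points; this is arithmetic and not a forecast. The matter deserves correction because adverse events are part of the primary feasibility outcome, the rule is fixed in the protocol itself, and the change is small.

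**What to change.** Reconcile sections E.5 and E.9 by adding to E.9 a statement to this effect: withdrawal from the intervention or the assessments does not by itself end safety recording. With permission given in the consent form, and unless the participant refuses all contact, an adverse event open at withdrawal is followed by telephone until its outcome and final seriousness are recorded. The participant is also asked about new events. All such events are counted in the arm to which the person was randomised.

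The on-trial logging window in E.5 should be worded to match, and the consent form needs a corresponding line.

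The cost is a short protocol and consent amendment and a few brief telephone calls, at most about 10 participants to contact at the target retention. The safety record may turn out somewhat less favourable.
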